# Direct-to-Implant Extracellular Matrix Hammock-based Breast Reconstruction; Prepectoral or Subpectoral?

**DOI:** 10.1186/s13063-020-4125-6

**Published:** 2020-02-10

**Keywords:** Breast animation deformity, Immediate breast reconstruction, Breast implants, Subpectoral implant placement, Prepectoral implant placement

## Abstract

**Background:**

Skin-sparing mastectomy followed by immediate implant-based breast reconstruction is a commonly used treatment for breast cancer. However, when placing the implant in a subpectoral pocket, a high incidence of breast animation deformity (BAD) has been reported. Besides the nuisance that BAD can cause, lifting of the pectoralis major muscle (PMM) can result in a more extended postoperative recovery period. When placing the implant solely prepectorally leaving the PMM undisturbed, the incidence and severity of BAD might be mitigated. However, new challenges may occur because of thinner skin cover.

**Methods/design:**

A prospective, multi-centre, randomised controlled trial will be carried out with the primary aim of assessing and comparing the incidence and degree of BAD in women having a direct-to-implant breast reconstruction with either a prepectorally or a subpectorally placed implant. The secondary outcomes are shoulder and arm function, quality of life, aesthetic evaluation, length of stay, complications, need for surgical corrections, and development of capsular contracture. A total of 70 included patients will be followed under admittance and at clinical check-ups 3 months and 1 year after surgery.

**Discussion:**

To our knowledge, this trial is the first randomised controlled trial evaluating and comparing subpectoral and prepectoral implant placement when performing direct-to-implant breast reconstruction following skin-sparing mastectomy. The results will hopefully provide us with a broader knowledge of the outcomes of immediate breast reconstruction, making better preoperative planning possible in the future by providing our patients with a more objective information.

**Trial registration:**

ClinicalTrials.gov, ID: NCT03143335. Prospectively registered on 8 May 2017.

## Background

Mastectomy is frequently used in breast cancer treatment and increasingly performed prophylactically as a risk-reducing intervention as either a skin-sparing mastectomy or a nipple-sparing mastectomy. Due to recent technical advances, the mastectomy procedure is more conservative than before and increasingly allows for immediate breast reconstruction [1, 2]. In immediate breast reconstruction, an implant is often placed below the pectoralis major muscle (PMM) caudally supported by a biological or synthetic mesh [3–5]. The hammock method was introduced by Salzberg and Breuing more than a decade ago [6–9].

Breast animation deformity (BAD), also referred to as breast distortion or ‘jumping breast’, is characterised by an unsightly deformation of the whole breast, breast skin or nipple-areolar complex [10]. The consequences of BAD have been described in cosmetic surgery following subpectoral breast augmentation by Spears in 2009 [11] although have not been widely addressed until recently.

Spears evaluated 40 breast-augmented women with a subpectoral positioning of the implant, which revealed that 77.5% had some kind of distortion during PMM contraction [11]. The theory is that BAD occurs due to the pressure applied by the contracting PMM on the underlying implant. There is a reason to believe that the severity of BAD may be more pronounced in women having a direct-to-implant breast reconstruction; there is less soft tissue to camouflage the muscle and underlying implant.

Breast reconstructions using subpectorally placed implants have been the mainstay until 2014 when prepectoral implant placement in combination with a synthetic titanium-coated mesh was introduced [12]. In prepectoral breast reconstruction, the implant lies above the PMM without disrupting the muscle. The aesthetic outcome of prepectoral implant-based breast reconstruction is comparable to the subpectoral techniques [13, 14]. The question is whether the PMM is needed for implant-based breast reconstruction. Data comparing the cosmetic and functional outcomes of prepectoral or subpectoral breast reconstruction is scarce. It seems that BAD may be prevented by placing the implant in the prepectoral plane. However, this has not been tested in a randomised clinical trial.

In this study, we compare the degree of BAD in patients having a direct-to-implant breast reconstruction using either subpectoral or prepectoral implant placement. The primary outcome measure of our study is the degree of BAD, assessed by the NSE scale [15]. There are currently other trials ongoing concerning immediate breast reconstruction and prepectoral placement of the implant. The trials are investigating different primary outcomes to our study. The trial with ClinicalTrials.gov identifier NCT02830685 aims to test whether there is a difference in outcomes between biological and synthetic mesh when placed as a support under the skin flaps when performing direct-to-implant prepectoral breast reconstruction. The primary outcome measures are surgical complications and technique failure. The trial with identifier NCT02831426 aims to test whether there is a difference in the outcomes between using biological and synthetic mesh when performing two-stage tissue-expander prepectoral breast reconstruction. The primary outcome measures are surgical complications and technique failure.

Furthermore, a breast reconstruction evaluation study is running; ISRCTN11898000, evaluating the safety of prepectoral breast reconstruction with the primary outcome measure being implant loss rate at 3 months.

The secondary aims in our study are to assess the functional and cosmetic outcomes between subpectorally and prepectorally reconstructed groups and to evaluate the patients-related outcome.

## Methods/design

### Study objectives

The primary outcome of this randomised controlled trial is the degree of BAD, assessed by the NSE scale [15]. The degree of BAD, will be assessed by two plastic surgeons viewing videos recorded at 12-month follow-up. In cases of disagreement, a consensus will be reached.

The primary objective of this study is to compare the degree of BAD between two groups of patients having a direct-to-implant breast reconstruction, randomised to either subpectoral implant placement or prepectoralimplant placement. The secondary objectives and comparisons between groups are: (1) assessment and comparison of the shoulder and arm function by use of the Constant Shoulder Score (CSS), (2) assessment and comparison of quality of life (QOL) by Breast-Q, (3) assessment of postoperative pain by the patients during the first three postoperative days using a visual analogue scale from 0 to 10, (4) comparison of time to discharge, (5) comparison of time for surgery, (6) registration and comparison of complications, major and minor, (7) aesthetic outcome evaluated by two consultant plastic surgeons, (8) assessment and comparison of the degree of capsular contracture and (9) identification of new breast cancer and breast cancer recurrence after 3 years registered in the National Patient Registry [16].

### Design of the study

This study is a prospective, randomised, multi-centre trial with two arms. After giving informed consent to participate in this study, patients are randomised to either subpectoral or prepectoral placement of the implant. In bilateral cases, both breasts are randomised as one case. All included patients will be followed under admittance and at clinical check-ups after 3 months and 1 year of reconstruction. Trial participants will not receive any compensation or remuneration for their participation in the trial. We will conduct the protocol of this trial according to the Standard Protocol Items: Recommendations for Interventional Trials (SPIRIT) guidelines (Additional file 1) [17]. The trial schedule is shown in Fig. 1

**Fig. 1 Fig1:**
[figure not shown]
Participant timelines

### Sample size

A non-parametric calculation of the sample size was made based on our assumptions and experience regarding the degree of BAD in the two groups. We used Fisher’s exact test for small sample sizes. Based on our experience we expected that approximately 60% of the patients who are reconstructed using subpectoral implant placement would suffer from BAD as opposed to 20% of the women who are reconstructed using prepectoral implant placement. By using these assumptions in combination with a significance level of 0.05 (one-sided) and a power of 0.95, the total sample size was calculated to 70 patients, 35 women in each group.

However, a retrospective cohort study in women over 18 years of age who had a unilateral or bilateral direct-to-implant breast reconstruction between November 2011 and December 2017 suggested the above sample size assumptions to be too conservative [15]. Therefore, we will conduct an interim analysis with 60% of the patients included (i.e. 0.6 × 70 = 42). The primary hypothesis will be tested conservatively with *n* = 42 patients applying an O’Brien-Fleming type α-spending function (i.e. α_1_^*^ in [18]), resulting in a significance level of 0.0114 at interim and securing an experiment-wise type 1 error of maximal 0.05.

The sample size is calculated using STATA, version 14.0 (StataCorp, College Station, TX, USA) using a two-sample proportion test.

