### Statistical analysis

We will conduct all our analysis using STATA (StataCorp, College Station, TX, USA). We use baseline variables to describe characteristics of the trial participants. Continuous variables are expressed as mean and standard deviations or as median and interquartile range (25th to 75th percentiles) if the distribution is asymmetrical. Categorical variables are summarised as numbers and percentages. We will compare the categorical variables between groups with a chi-squared test or Fisher’s exact test depending on the number of events. We will compare the continuous variables between groups using an unpaired *t* test or a Mann-Whitney *U* test depending on data representation. A two-sided *p* value of less than 0.05 will be considered significant and reported with a 95% confidence interval. The consistency between different surgeons’ evaluations of BAD and aesthetics will be evaluated using kappa statistics testing the inter- and intrarater reliability [27]. The primary outcome is the proportion of patients with BAD in the subpectorally and prepectorally reconstructed groups. We will compare between groups using the chi-squared test or Fisher’s exact test and a *p* value of less than 0.05 will be considered significant.

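### The trial is sized for a one-sided 0.05 test but analysed two-sided at 0.05, so 35 per arm gives a power of about 0.91 (Fisher) or 0.94 (chi-squared), not the stated 0.95

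*Protocol article*

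**What the plan says.** The Sample size section of the protocol article assumes breast animation deformity in about 60% of subpectoral and 20% of prepectoral patients. The calculation reads: "a significance level of 0.05 (one-sided) and a power of 0.95, the total sample size was calculated to 70 patients". This is 35 per arm.

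The section describes the sizing method twice. Near the start it says "We used Fisher’s exact test for small sample sizes"; its last sentence says that the calculation was done in Stata "using a two-sample proportion test".

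It also plans an interim analysis of the primary hypothesis at 42 patients, at a level of 0.0114 from an O'Brien-Fleming type spending function, with an overall type 1 error of at most 0.05. It does not say whether 0.0114 is one- or two-sided.

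The Statistical analysis section states: "A two-sided *p* value of less than 0.05 will be considered significant". It then gives the primary comparison as a chi-squared or Fisher's exact test at 0.05. That sentence does not repeat the word two-sided, but it does not depart from the general rule either.

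**The concern.** A power figure belongs to a particular test at a particular level. Here the 0.95 belongs to a one-sided test at 0.05, and the analysis rule is two-sided at 0.05, which puts 0.025 in the tail of interest. The planned analysis is therefore stricter than the one that was sized, and the stated power cannot carry over to it.

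Two things are at stake. First, the article credits the design with a type 2 error of 5% that its analysis rule does not have. Second, the decision rule is open. A result in the expected direction with a one-sided p of 0.04 has a two-sided p of about 0.08: significant under the rule used for sizing, not significant under the rule in the analysis section. That should be settled before any efficacy look, and one is planned at 42 patients.

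The two descriptions of the sizing method add a smaller problem. A reader who follows the closing sentence with the usual uncorrected formula will not arrive at 70.

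**Working it through.** **Inputs, all from the Sample size section:** p1 = 0.60, p2 = 0.20, difference d = 0.40, mean 0.40, equal arms, 35 per arm, power 0.95 (z = 1.645), one-sided alpha 0.05 (z = 1.645). From the Statistical analysis section: two-sided alpha 0.05 (z = 1.960).

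**1. Reproducing 70.** Exact power is the sum of the product of the two binomial probabilities over all tables that the test rejects. For one-sided Fisher at 0.05:
- 34 per arm: 0.949
- 35 per arm: 0.957

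The target of 0.95 is reached at 35 per arm, so 70 in total, as stated.

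**2. The two-sample proportion test.** With pooled variance under the null, n per arm = [z_alpha × √(2 × 0.40 × 0.60) + z_beta × √(0.60 × 0.40 + 0.20 × 0.80)]² / 0.40².
- One-sided: (1.645 × 0.6928 + 1.645 × 0.6325)² / 0.16 = 2.180² / 0.16 = 29.7, so 30 per arm, 60 in total.
- Two-sided: (1.960 × 0.6928 + 1.645 × 0.6325)² / 0.16 = 2.398² / 0.16 = 35.9, so 36 per arm, 72 in total.

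With the continuity correction, n_c = (n/4) × [1 + √(1 + 4/(n × d))]²:
- One-sided: 34.5, so 35 per arm, 70 in total.
- Two-sided: 40.8, so 41 per arm, 82 in total.

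Hence 70 follows from one-sided Fisher or the one-sided continuity-corrected formula. The uncorrected proportion test gives 60 one-sided and 72 two-sided.

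**3. Power of the two-sided analysis at 35 per arm, by exact enumeration at 0.05:**

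| Test | Power | Type 2 error | Below 0.95 by |
|---|---|---|---|
| Fisher | 0.910 | 9.0% | 4.0 points |
| Chi-squared, uncorrected | 0.942 | 5.8% | 0.8 points |

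To reach 0.95 two-sided, Fisher needs 41 per arm (0.947 at 40, 0.954 at 41) and chi-squared needs 37 (0.949 at 36, 0.951 at 37).

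**4. Allowing for the interim.** The spending function 2 × [1 − Φ(1.960/√0.6)] gives 0.0114, matching the article. Spending 0.025 separately in each tail would give 0.0076, so the figure alone does not settle the sidedness. If 0.0114 is read as a two-sided level at 60% information, the final two-sided level that keeps 0.05 overall is about 0.0457. With looks at 21 and 35 per arm, overall power is about 0.90 for Fisher and 0.94 (0.938) for chi-squared.

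**5. Missing 12-month videos (an assumption, not in the article).** If 10% had no assessment, leaving 31 or 32 per arm, two-sided power without the interim would be 0.870 or 0.887 for Fisher and 0.918 or 0.930 for chi-squared.

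**The case against.** The strongest reply is that little is lost. The Statistical analysis section lets the number of events decide between chi-squared and Fisher for categorical variables. At the design rates, 35 per arm means about 21 and 7 events (35 × 0.60 and 35 × 0.20), so the smallest expected cell is (21 + 7)/2 = 14. That points to chi-squared, where the shortfall is under one point. A two-sided rule is also stricter, so the type 1 error is not harmed. The article adds that retrospective data made its assumptions look too conservative; at 65% versus 20%, chosen only for illustration, two-sided power at 35 per arm would be 0.961 (Fisher) and 0.977 (chi-squared). All of this stands. It limits the size of the problem but does not reconcile the two sections: at the article's own 60% and 20%, neither named test reaches 0.95 two-sided.

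On the sizing method, Fisher's test is itself a comparison of two proportions, and the closing sentence may only describe the software routine. That is a fair reading, so this part is a matter of clarity.

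A reader might infer three stronger things that the article does not support:
- **That 70 is an arithmetic error, or that the named test does not give it.** One-sided Fisher, which the section names, gives exactly 70.
- **That the type 2 error is nearly doubled whatever test is used.** That holds only for Fisher (9.0% against 5%); with chi-squared it is 5.8%.
- **That losses to follow-up push power below 0.90.** The 10% is an assumed rate, and the absence of an attrition allowance from a condensed article is not a misstatement. Even at that rate, chi-squared power without the interim stays above 0.91.

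**Conclusion.** The point holds as an inconsistency of sidedness. The power of 0.95 is correct for a one-sided Fisher test at 0.05 with 35 per arm and is not delivered by the two-sided analysis that the article sets out. The interim, on the reading in step 4 of the working, changes the result by less than one point.

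This rests on the article's 60% and 20%, on 35 evaluable patients in each arm (simple randomisation does not guarantee an equal split), and on applying the general two-sided rule to the primary outcome, whose own sentence is silent on sidedness. The trial stays well powered on these assumptions, and nothing here shows that 70 patients are too few. It is worth correcting because the decision rule is ambiguous and the stated power is untrue for the stated analysis, but it is not a serious design fault.

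**What to change.** Keep 70 patients and change the wording:

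- State one sidedness, two-sided as in the Statistical analysis section, for the sample size, the interim level and the final test. Say explicitly whether 0.0114 is two-sided, and give the final level that goes with it (about 0.0457 if it is).
- Name one primary test in place of the choice between chi-squared and Fisher.
- Restate the power for that test at 35 evaluable patients per arm, including the interim: about 0.90 for Fisher's exact test or about 0.94 for the uncorrected chi-squared test. Say that 70 was originally obtained from a one-sided calculation.
- Correct the closing sentence of the Sample size section so that it names the method that gave 70. On these numbers that is Fisher's exact test, or a continuity-corrected formula, one-sided.
- Label any power figure that allows for missing 12-month videos as resting on an assumed loss rate.

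The cost is wording and a stated power that is slightly less favourable. No extra patients are needed, and the design does not change.

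### The final primary test keeps the full 0.05 after 0.0114 has been spent at the interim, so the claimed overall type 1 error limit of 0.05 is not secured

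*Protocol article*

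**What the plan says.** Under Sample size, the protocol article assumes BAD rates of 60% in the subpectoral arm and 20% in the prepectoral arm. The design parameters are "a significance level of 0.05 (one-sided) and a power of 0.95". They lead to 35 patients per arm, 70 in all. The section then adds an interim test of the primary hypothesis at 42 patients, based on an O'Brien-Fleming-type spending function, and describes the effect of this as "resulting in a significance level of 0.0114 at interim and securing an experiment-wise type 1 error of maximal 0.05". It gives no level for the final analysis.

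The Statistical analysis section names the primary outcome (the proportion of patients with BAD) and its test (chi-squared or Fisher's exact). Its decision rule is that a p "value of less than 0.05 will be considered significant". A general sentence earlier in the same section makes the 0.05 threshold two-sided. The section does not mention the interim look or a lower final threshold.

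**The concern.** An alpha-spending function divides a fixed total error between the looks. If 0.0114 is used at the interim, only 0.05 − 0.0114 = 0.0386 remains for rejecting at the end having not rejected at the interim. Because the two test statistics are correlated, this remainder corresponds to a final nominal level somewhat above 0.0386, but it must be below 0.05. The Statistical analysis section leaves it at 0.05. The guarantee in one section and the decision rule in the other are therefore incompatible for a test that attains its nominal level.

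At stake is the primary conclusion when the trial runs to 70 patients and the final two-sided p lies between about 0.0457 and 0.05. The written rule would call that result significant; the sequential design would not.

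**Working it through.** **Inputs.** From Sample size: overall error 0.05, information fraction t = 42/70 = 0.6, interim level 0.0114, 35 patients per arm, BAD rates 60% and 20%. From Statistical analysis: final level 0.05, chi-squared or Fisher's exact test. Assumptions of this check: equal arms (21 per arm at the interim, 35 at the end), and Fisher's test whenever an expected count is below 5. The document says only that the choice depends on the number of events.

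**1. The plan's interim level.** The O'Brien-Fleming-type function is α(t) = 2 − 2Φ(z₀.₉₇₅/√t). With t = 0.6:

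2 − 2Φ(1.95996/√0.6) = 2 − 2Φ(2.530) = 0.011396, which rounds to 0.0114. The plan's figure is reproduced.

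**2. Overall error with the rules as written.** Under the null hypothesis the interim and final statistics Z₁ and Z₂ are bivariate standard normal with correlation √0.6 = 0.775.

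- Both looks two-sided: P(|Z₁| > 2.530 or |Z₂| > 1.960) = 0.0541.
- Both looks one-sided, at 0.0114 and 0.05: 0.0533.

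Both exceed 0.05, by 0.41 and 0.33 percentage points.

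**3. Final level that would hold 0.05.** Solve P(|Z₁| > 2.530 or |Z₂| > c) = 0.05 for c. The result is c = 1.9985, a two-sided p of 0.0457. If both looks were one-sided, the final level would be 0.0465.

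**4. Exact check.** Two-stage binomial enumeration, two-sided tests, over common BAD rates from 0.02 to 0.98. Maximum overall error:

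| Test rule | No interim, 0.05 | 0.0114 then 0.05 | 0.0114 then 0.0457 |
|---|---|---|---|
| Chi-squared, Fisher's if an expected count < 5 | 0.0520 | 0.0562 | 0.0521 |
| Chi-squared always | 0.0574 | 0.0585 | 0.0527 |
| Fisher's always | 0.0294 | 0.0314 | 0.0289 |

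At a common rate of 40%, the mean of the two planning rates, the first rule gives 0.0484 without an interim, 0.0528 with 0.0114 then 0.05, and 0.0481 with 0.0114 then 0.0457. There the unadjusted interim alone takes the error past 0.05, and the lower final level brings it back.

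**5. Which test is likely.** At a pooled rate of 40%, the expected number of BAD cases per arm is 0.4 × 21 = 8.4 at the interim and 0.4 × 35 = 14 at the end. Both are above 5, so under the usual convention chi-squared would be used.

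**6. Power cost at 60% against 20%**, by the same enumeration over both looks: moving the final level from 0.05 to 0.0457 changes power from 0.944 to 0.938 with chi-squared and from 0.912 to 0.903 with Fisher's test.

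**The case against.** **The final boundary is implied.** Once the total error, the spending function and the information fraction are fixed, the final boundary follows. The 0.05 in the analysis section could then be read as the overall level, with the nominal boundary left to an SAP that is not shown. This would be persuasive if the article were silent. It is not: it attaches an explicit p-value threshold to the primary outcome, and an SAP with a lower level would contradict it.

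**Fisher's test protects the trial.** If Fisher's test were used at both looks, the error would be about 0.031 and the guarantee would hold even with 0.05 at the end. That is correct, but the plan equally allows chi-squared. The cut-off of 5 used here to judge which test applies is a convention, not the plan's own rule.

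**The exact maximum overstates the effect.** This stands in part. Of the 0.0562, 0.0520 is present with no interim at all, and the corrected level still gives 0.0521. That remainder comes from the chi-squared approximation in small samples; the interim adds about 0.004. The enumeration also assumes equal arms, whereas the plan uses simple randomisation. The normal-approximation figure of 0.0541 is the one that isolates the fault.

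**Sidedness is unsettled.** The sample size is one-sided and the analysis two-sided, and the plan does not say which applies to 0.0114. This affects the exact replacement level (0.0457 or 0.0465) but not the finding. If the interim were one-sided at 0.0114 and the final test two-sided at 0.05, the error favouring prepectoral placement alone would be about 0.030, but over both directions it would be about 0.055.

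**The excess is small.** This is true. It changes a conclusion only in a narrow band of final p values.

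**Conclusion.** The concern holds. The interim level of 0.0114 is correct, but together with a final p < 0.05 it gives an overall type 1 error of about 0.054 two-sided (0.053 one-sided) instead of at most 0.05. This rests on the normal approximation, one interim at information fraction 0.6, and the same sidedness at both looks. The limit would be met with an unreduced final level if Fisher's exact test were used throughout, but the plan does not commit to that. The size is modest, about 0.3 to 0.4 percentage points. It still needs correcting, because the plan states a firm ceiling for its primary test and its own decision rule does not respect it.

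**What to change.** Replace the final criterion for the primary outcome in the Statistical analysis section. Suggested wording: *If the interim analysis is performed on 42 of 70 evaluable patients at a two-sided level of 0.0114, the final comparison of the proportion with BAD is significant at a two-sided p < 0.0457 (|Z| ≥ 1.9985). If the information fraction at the interim differs from 0.6, both levels are recomputed from the same spending function. If no interim analysis is performed, the final level is 0.05.*

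State in both sections that the thresholds apply to two-sided p values, in line with the two-sided rule already in the analysis section. If the trial team instead chooses one-sided testing at both looks, the corresponding final level is 0.0465 and both sections must say so.

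The cost is one short addition to the text. Sample size, data collection and the interim level do not change, and the loss of power is under one percentage point. The article reports that the trial is still enrolling; the change should be made before any comparative results are seen.
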